### Information from the medical record

The information which will be obtained in the medical record are listed in Table 1.

**Table 1 Information to be obtained from the medical record**

| Time of collection       | Variables i medical record                                             | Purpose                            |
|--------------------------|------------------------------------------------------------------------|------------------------------------|
| Prior ED arrival         | Antibiotic treatment within last 6 months                              | Confounding                        |
| Upon ED arrival          | Vital signs                                                            | Patient characteristic             |
|                          | Triage                                                                 | Patient characteristic             |
|                          | Comorbidity                                                            | Patient characteristic             |
|                          | Antibiotic allergy                                                     | Patient characteristic             |
|                          | Inhalation medication                                                  | Confounding                        |
| During admission         | Prescribed antibiotic                                                  | Outcome                            |
|                          | Blood test results                                                     | Patient characteristic             |
|                          | Microbiological test results of blood, urine, swab and sputum          | Outcome                            |
|                          | Diagnostic imaging results                                             | Outcome                            |
|                          | ICU transfer                                                           | Outcome                            |
|                          | Findings regarding diagnosis and treatment described in clinical notes | Outcome and patient characteristic |
|                          | Date of discharge                                                      | Outcome                            |
| After hospital discharge | Date of mortality                                                      | Outcome                            |
|                          | Date of readmission                                                    | Outcome                            |

|  |                   |         |
|--|-------------------|---------|
|  | C. diff infection | Outcome |
|--|-------------------|---------|

## Outcomes and statistical analysis

Before data analysis, data will be pseudonymised. Datamanagement and statistical analysis will be performed in STATA.

Annually, 5.7% of patients are diagnosed with pneumonia and 2.4% with pyelonephritis (data from the ED at Hospital Sønderjylland). Taking into account exclusion criteria, weekends/holidays/missing data and experience in patient recruitment, it is estimated that at least 1000 patients admitted with suspected infection must be included in the study from the three hospitals over a 7-month period, of which at least 250 patients will be diagnosed with pneumonia and at least 150 patients with pyelonephritis.

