## Setting

The study will recruit patients from here regional hospitals in the Region of Southern Denmark: the ED in Kolding, Lillebælt Hospital, the ED in Aabenraa, Hospital Sønderjylland, and the ED in Odense, Odense University Hospital. Six study assistants are associated to the study to ensure patient recruitment and data collection. They will be trained and certified in US of lung and kidneys (Objective Structured Assessment of Ultrasound Skills (OASUS) test), sputum collection, operation and integration of POC-PCR as well as POC urine flow cytometry.

Enrollment to the study commences from February 2021, and continues until the predefined sample size has been reached, which is estimated to be no longer than eight months. The last patient is expected to be enrolled in the end of September 2021. The patients will be enrolled from Sunday to Friday 10am-8pm except on holidays.

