### *Patient characteristics and course of treatment*

Patient characteristics according to pre-defined clinical parameters will be noted in REDCap. The parameters include symptoms, signs, disease severity, vital signs, triage at arrival, comorbidities, functional status, resident status, antibiotics prescribed during the last 6 months and medical history.

Logistic univariate and multivariate analysis will be carried out for selected risk indicators of pneumonia or pyelonephritis. For pneumonia diagnosis at least 15 variables have to be analyzed, and 200 patients with verified diagnosis are needed (50+15 events/variable). For pyelonephritis at least 10 variables have to be analyzed, and 150 patients with verified diagnosis are needed (50+10 events/variable). (44)

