### *Diagnostic value of POC urine flow cytometry*

Common urinary culture shows significant growth of uropathogenic bacterium in approximately 50% of people with suspected pyelonephritis (30). Asymptomatic bacteriuria accounts for about 20% in the elderly population, depending on gender and age (46), which among 1000 inpatients suspected of infection, of which 15% have pyelonephritis, gives a sensitivity of 50% (95% CI: 42-58 %) and a negative predictive value of 90% (95% CI: 77-83%). With the expectation of identifying at least 150 cases of pyelonephritis among 750 inpatients suspected of infection, an improvement in sensitivity to 70% (95% CI: 62-77%) and negative predictive value to 95% (95% CI: 93 -96%) could be found with 95% security.

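### The pyelonephritis case basis is inconsistent: the flow-cytometry section uses both 15% of 1000 and 150 of 750, its 95% NPV is impossible on the second, and the 150 cases are neither derived nor given a margin

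*Protocol*

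**What the plan says.** Outcomes and statistical analysis gives one source for the case mix: "Annually, 5.7% of patients are diagnosed with pneumonia and 2.4% with pyelonephritis (data from the ED at Hospital Sønderjylland"). It then sets a total of 1000 or more, drawn from three hospitals in seven months, and gives the case counts within that total as minima: "of which at least 250 patients will be diagnosed with pneumonia and at least 150 patients with pyelonephritis". The allowances are named without figures: "Taking into account exclusion criteria, weekends/holidays/missing data and experience in patient recruitment".

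Patient characteristics and course of treatment asks for 10 candidate variables for pyelonephritis, for which "150 patients with verified diagnosis are needed (50+10 events/variable"). For pneumonia it asks for 15 variables and 200 verified cases. Diagnostic value of infection markers again needs 150 verified pyelonephritis cases (with 150 controls) and 200 verified pneumonia cases (with 200 controls).

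Diagnostic value of POC urine flow cytometry takes 1000 inpatients of whom 15% have pyelonephritis, with sensitivity 50% and NPV 90%. The target sentence changes the denominator: "With the expectation of identifying at least 150 cases of pyelonephritis among 750 inpatients suspected of infection". It gives a sensitivity of 70% (62 to 77%) and an NPV of 95% (93 to 96%).

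Setting says that enrolment "continues until the predefined sample size has been reached", without saying whether that size counts patients or cases.

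**The concern.** An NPV depends directly on the share of patients with the disease. A section that moves from 15% to 20% between its baseline and its target therefore does not compare like with like, and its target may not be arithmetically possible. Ruling out bacteriuria is the stated purpose of the flow-cytometry test, so the NPV is the figure that matters most there.

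The 150 is also the figure on which the 10-variable regression and the marker comparison are sized. If it does not follow from the quoted rates, and if every diagnosed case has to be verified to reach it, those two sizes have no visible support.

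**Working it through.** **1. Flow cytometry: shares and NPV.**

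Inputs from the flow-cytometry section: 1000 patients at 15%; 150 cases among 750; sensitivity 50% at baseline and 70% as target. Specificity is not stated. A baseline value of 80% is my reading of the 20% asymptomatic bacteriuria quoted there.

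Shares: 150/1000 = 15%; 150/750 = 20%; 15% of 750 = 112.5.

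The plan's own figures first. Sensitivity 70% with 150 cases gives a 95% interval of 62 to 77%, as printed. Baseline NPV on 1000: true negatives 850 × 0.8 = 680, false negatives 150 × 0.5 = 75, NPV = 680/755 = 90.1%, matching the printed 90%. Its 95% interval, however, is 88 to 92%; the printed 77 to 83% does not contain its own estimate.

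Target NPV = TN/(TN + FN), with FN = 150 × 0.3 = 45:

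| Denominator | Specificity | NPV | 95% interval |
|---|---|---|---|
| 750 (20%) | 100% | 600/645 = 93.0% | 91 to 95% |
| 750 (20%) | 80% | 480/525 = 91.4% | 89 to 94% |
| 1000 (15%) | 100% | 850/895 = 95.0% | 93 to 96% |
| 1000 (15%) | 80% | 680/725 = 93.8% | 92 to 95% |

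The printed 95% (93 to 96%) reproduces at a 15% share with perfect specificity. On 150 of 750 it is out of reach at any specificity.

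**2. The 150 against the cited rates.**

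Inputs: 5.7%, 2.4%, 1000, 250 and 150, all from Outcomes and statistical analysis. I read the rates as shares of all ED patients. Let s be the share of ED patients with suspected infection, which is not stated.

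- Ratio: 2.4/5.7 = 0.421. Beside 250 pneumonia cases: 250 × 0.421 = 105. Conversely, 150/0.421 = 356 pneumonia cases.
- Implied s: 5.7/25 = 22.8% from the pneumonia count, 2.4/15 = 16.0% from the pyelonephritis count.
- Yield per 1000 is 24/s for pyelonephritis and 57/s for pneumonia: 200 and 475 at s = 12%, 150 and 356 at 16%, 120 and 285 at 20%, 105 and 250 at 22.8%, 80 and 190 at 30%.

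The rates give 150 only if s is 16% or less.

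**3. Diagnosed against verified.**

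The regression sizes reproduce as 50 plus 10 per variable: 50 + 10 × 10 = 150 and 50 + 10 × 15 = 200. Surplus of diagnosed over verified: pneumonia 250 − 200 = 50; pyelonephritis 150 − 150 = 0.

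No confirmation rate is given, so these are assumed values:

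| Confirmation rate | Verified of 150 | Whole variables, (n − 50)/10 | Diagnosed needed for 150 verified |
|---|---|---|---|
| 90% | 135 | 8 | 167 |
| 80% | 120 | 7 | 188 |
| 70% | 105 | 5 | 215 |
| 50% | 75 | 2 | 300 |

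Even with a true share of exactly 15% and full confirmation, the chance of at least 150 cases in 1000 is 51%.

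**4. Marker comparison.**

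For AUC 0.6 against 0.7 at 80% power and two-sided 5%, the cases needed (with as many controls) run from 121–122 at a correlation of 0.5 between the markers to 242–244 with none; one-sided, from 96 to about 192. The stated 150 lies inside this range, but the Protocol gives neither sidedness nor correlation, so the effect of a shortfall cannot be fixed to one number.

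**The case against.** Both case counts are minima. If pyelonephritis is the limiting condition, the cited rates give 150 pyelonephritis and 356 pneumonia cases, and both minima are met. The rates come from one ED, while the 1000 are consenting patients with suspected infection at three hospitals, so the 5.7 to 2.4 ratio need not carry over. The Protocol says that exclusions, missing data and recruitment experience were considered. All of this stands. It rules out saying that 150 cannot be reached, but it does not supply the missing derivation.

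The loss from diagnosed to verified is also assumed. The background says that up to half of clinical cases lack significant bacteriuria, but the imaging section uses an expert panel, and the planned diagnosed count may already mean the panel's diagnosis. That stands too. Even then, the plan needs every one of its 150 expected cases, and the regression and marker sections do not say which meaning of verified applies.

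A reader might infer a real loss of flow-cytometry sensitivity precision. The figures do not support that: with 105 cases the interval is 61 to 78%, against 62 to 77%, and that section does not ask for verified cases. A reader might also infer that the MRI and contrast exclusions shrink the count further. Those exclusions are listed for track B only, whereas the regression, marker and flow-cytometry analyses use records, blood and urine taken from all participants, and consent can be given to individual parts.

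None of these points touches the NPV.

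**Conclusion.** The flow-cytometry target is wrong as written. With 150 cases among 750 and 70% sensitivity, the NPV is at most 93.0%, not 95% (93 to 96%). This assumes nothing about specificity. The printed value requires a share of about 15% and near-perfect specificity, whereas the baseline NPV of 90% fits a specificity of 80%.

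The 150 is unsupported rather than refuted. Set beside 250 pneumonia cases, the quoted rates give about 105, and the plan leaves no surplus over the verified cases it needs. The regression and marker sizes are therefore at risk. A stronger reading, that the 150 will not be delivered, is tempting, but the documents do not show it: it would need a suspected-infection share above 16% and a known confirmation rate, and neither is given. For the same reason 105, or 84 if the pneumonia ratio of 200/250 is borrowed (0.8 × 105), are illustrations and not replacement values.

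**What to change.** - Use one pyelonephritis share and one denominator in Outcomes and statistical analysis and in the flow-cytometry section. Recompute the baseline and target NPV and their intervals on them, with the assumed specificity stated.
- In Outcomes and statistical analysis, give the suspected-infection share and the expected confirmation rate behind the 150.
- Define what verified means in the regression and marker sections.
- If the expected verified count is below 150, restate those two sections on it: fewer candidate variables under the rule of 50 plus 10 per variable, and the detectable AUC difference or the power, with the assumed correlation and sidedness.
- In Setting, say whether the predefined size counts patients or verified cases.

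The cost is wording. The stated NPV, and possibly the number of variables and the power, become less favourable. No extra patients follow from the correction itself; ending enrolment on verified cases could require more than 1000, so that choice should be made knowingly.

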### *Patient characteristics and course of treatment*

Patient characteristics according to pre-defined clinical parameters will be noted in REDCap. The parameters include symptoms, signs, disease severity, vital signs, triage at arrival, comorbidities, functional status, resident status, antibiotics prescribed during the last 6 months and medical history.

Logistic univariate and multivariate analysis will be carried out for selected risk indicators of pneumonia or pyelonephritis. For pneumonia diagnosis at least 15 variables have to be analyzed, and 200 patients with verified diagnosis are needed (50+15 events/variable). For pyelonephritis at least 10 variables have to be analyzed, and 150 patients with verified diagnosis are needed (50+10 events/variable). (44)

### *Diagnostic value of infection markers*

The concentration of PCT, CRP, and suPAR are evaluated for the verified diagnosis of pneumonia/pyelonephritis and compared to a control group using receiver-operating characteristic (ROC) curves and identifying an optimal cut-off. Secondary outcomes will evaluate which infection marker in combination of severity scores can assess disease severity and predict short-term and long-term mortality in pneumonia patients.

The study is designed to be able to find a difference in Area under the curve (AUC) from 0.7 to 0.8 between two tests, which requires 200 verified pneumonia cases and 200 controls (power 0.8, alpha 0.05, AUC below 0 hypothesis 0.7) and 150 verified pyelonephritis cases and 150 controls (power 0.8, alpha 0.05, AUC below 0-hypothesis 0.6) (45).

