### ***Hypothesis, aim and objectives***

Our broad hypothesis is that by improving the knowledge of ED infected patients and by introducing new diagnostic tools, which contribute to the development of rapid and more accurate diagnosis of acute infections, a more appropriate antibiotic therapy can be administered.

The project aims to adapt and evaluate alternative diagnostic tools and working methods that support a prompt and accurate diagnosis of hospitalized patients suspected of an urgent infection – with special focus on pneumonia and acute pyelonephritis.

The research objectives are:

- 1) What is the patient characteristics and course of treatment of the different ED infections?
- 2) What is the diagnostic value of the infection markers PCT, suPAR, and CRP in patients with suspected pneumonia and pyelonephritis?
- 3) What is the diagnostic value of the lung injury markers SP-D, YKL-40, and KL-6 on diagnosing pneumonia
- 4) What is the impact of bedside-US and ULDCT on diagnosing pneumonia ?
- 5) What is the impact of advanced US on diagnosing pyelonephritis?
- 6) What is the impact of bedside-US on diagnosing hydronephrosis?
- 7) What is the impact of POC-PCR analysis of sputum on antibiotic prescriptions?
- 8) What is the impact of POC urinary flow cytometry on diagnosing and excluding bacteraemia?

The goal is to combine the results of all these eight objectives into one novel diagnostic model which the ED physician can apply when patients with suspicion of an infection is admitted.

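### Accuracy read at the data-chosen marker cut-offs would, if reported uncorrected from the same patients, be about 2 to 3 points too high per measure on average

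*Protocol*

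**What the plan says.** The second research objective asks: "What is the diagnostic value of the infection markers PCT, suPAR, and CRP in patients with suspected pneumonia and pyelonephritis"? It names no accuracy measure. The protocol's section Diagnostic value of infection markers gives the method. It begins with what is measured: "The concentration of PCT, CRP, and suPAR are evaluated for the verified diagnosis of pneumonia/pyelonephritis". It then says how the analysis is done: the values are "compared to a control group using receiver-operating characteristic (ROC) curves and identifying an optimal cut-off". That makes three markers and two diagnoses, each with a threshold derived from the study's own ROC curve. The section states no selection criterion, no fixed threshold and no separate evaluation sample.

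The quantity that is powered is the AUC: "The study is designed to be able to find a difference in Area under the curve (AUC) from 0.7 to 0.8 between two tests". For pneumonia this "requires 200 verified pneumonia cases and 200 controls (power 0.8, alpha 0.05, AUC below 0 hypothesis 0.7"); for pyelonephritis the figures are "150 verified pyelonephritis cases and 150 controls (power 0.8, alpha 0.05, AUC below 0-hypothesis 0.6"). Under Outcomes and statistical analysis the single cohort is expected to yield enough patients that "at least 250 patients will be diagnosed with pneumonia and at least 150 patients with pyelonephritis".

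Sensitivity and specificity are named as outcomes in the two imaging sections, not in the marker section.

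**The concern.** A cut-off that maximises some function of sensitivity and specificity in a sample partly follows that sample's chance features. Accuracy read at that point in the same sample is then too favourable on average. This comes from the maximising step itself and does not require any error in the assay or the reference diagnosis.

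What is at stake is any statement of the form that a marker at a given threshold has a given sensitivity and specificity. A cut-off is of little use to an emergency physician without such a statement, so it is natural to expect one. The error is systematic, so it also affects the confidence interval: a standard binomial interval treats the cut-off as if it had been fixed beforehand.

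**Working it through.** **1. Inputs.** From the marker section: 200 cases and 200 controls for pneumonia, 150 and 150 for pyelonephritis, AUC values of 0.7 and 0.8, and a pyelonephritis null AUC of 0.6. From Outcomes and statistical analysis: at least 250 and at least 150 expected cases. Assumed, because the protocol gives neither: a cut-off that maximises the Youden index J = sensitivity + specificity − 1, and normally distributed markers with equal variance in cases and controls.

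**2. The plan's own figure.** Compare two uncorrelated AUCs with the large-sample Hanley-McNeil variance V(A)/n, where V(A) = A/(2 − A) + 2A²/(1 + A) − 2A².

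- V(0.7) = 0.5385 + 0.5765 − 0.98 = 0.1349
- V(0.8) = 0.6667 + 0.7111 − 1.28 = 0.0978
- n = [1.96·√(2 × 0.1349) + 0.8416·√(0.1349 + 0.0978)]² / 0.1² = (1.018 + 0.406)² / 0.01 ≈ 203 per group

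The stated 200 is reproduced with two-sided alpha 0.05. The 150 per group for pyelonephritis cannot be checked, because its alternative AUC and the correlation between tests are not stated: 0.6 against 0.7 gives 244 per group uncorrelated, 171 at correlation 0.3 and 122 at 0.5. This has no bearing on the present point. No cut-off enters either calculation.

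**3. Room for a hold-out sample.** Pneumonia: 250 − 200 = 50 cases above the requirement. Pyelonephritis: 150 − 150 = 0. A separate evaluation sample is neither described nor budgeted.

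**4. Size of the optimism.** In each of 4,000 simulated data sets per setting, the Youden cut-off was chosen, and sensitivity and specificity in the sample were compared with their true values at that same cut-off. The interval checked is J ± 1.96·√[se(1 − se)/n₁ + sp(1 − sp)/n₀].

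| Cases/controls | True AUC | J in sample | True J at chosen cut-off | Excess sensitivity (points) | Excess specificity (points) | Coverage of nominal 95% interval | Interval wholly above truth |
|---|---|---|---|---|---|---|---|
| 200/200 | 0.7 | 0.321 | 0.280 | 2.1 | 2.0 | 86.7% | 13.3% |
| 200/200 | 0.8 | 0.474 | 0.439 | 2.0 | 1.5 | 87.3% | 12.6% |
| 150/150 | 0.7 | 0.327 | 0.278 | 2.5 | 2.4 | 85.9% | 14.1% |
| 150/150 | 0.6 | 0.189 | 0.130 | 3.1 | 2.7 | 83.6% | 16.4% |

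For true AUC from 0.6 to 0.9 the excess is 1.3 to 2.7 points per measure at 200/200 and 1.6 to 3.1 at 150/150. The in-sample J exceeded its true value in 79% to 90% of data sets. A correct interval would lie wholly above the truth in 2.5% of samples; here it does so about five times (12.6/2.5) to six and a half times (16.4/2.5) as often.

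**5. More controls.** If all non-cases served as controls (250/750, an assumption), the excess at AUC 0.8 is 1.9 points in sensitivity and 0.5 in specificity. At AUC 0.7 the interval coverage is still only 87.8%.

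**6. Ranking.** At 200/200, markers with AUC 0.8 and 0.7 differ in true J by 0.439 − 0.280 = 0.159 and in apparent J by 0.474 − 0.321 = 0.153. The bias is almost common to both.

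**7. Effect of the correction.** Bootstrap optimism correction, with the cut-off chosen afresh in each resample, removed about 70% to 77% of the bias. At 200/200 and AUC 0.7 it lowered the root mean squared error of J from 0.057 to 0.044.

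**The case against.** The strongest reply is that the marker section never says sensitivity and specificity at the cut-off will be reported, and never says that correction will be left out. The powered measure is the AUC. The choice of criterion and internal validation are commonly settled in a statistical analysis plan, which was not available here. This stands. A reader might infer that the protocol commits to reporting uncorrected accuracy; its text does not support that, and the point has to be conditional. What remains is that the optimising step is stated in the protocol, in one cohort with no evaluation sample, and that step creates the bias.

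The size can also be called small: the standard error of sensitivity at a fixed cut-off is about 3 to 4 points with 150 to 200 cases, so the bias is at or below one standard error. That is correct, but it does not repair the interval coverage. The relative excess at 150/150 and AUC 0.6, (0.189 − 0.130)/0.130 or about 45%, should not be used as a headline: it is a ratio to a very small index, for a marker that would hardly be recommended.

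Three further inferences fail. That the ranking of the markers is distorted is contradicted by step 6 of the working, and the planned comparison of tests is in any case by AUC. That the cut-offs are the main product of the second objective is not stated anywhere. That biased cut-offs pass into the final tool is not shown: the aim is to "combine the results of all these eight objectives into one novel diagnostic model", but the protocol does not say that dichotomised markers or their accuracies enter it, and the section Significance of the study plans to test that model later in at least eight emergency departments. That later test, for its part, does not correct marker accuracies reported from this study.

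**Conclusion.** The point holds in conditional form and is minor. If accuracy at a data-selected cut-off is reported from the same patients without correction, it will be too high on average, though not in every sample: about 2 points per measure at 200/200 and up to about 3 at 150/150. Ordinary 95% intervals for the Youden index will cover about 84% to 87%, with nearly all misses on the flattering side. The AUC comparisons and the sample size are untouched. The sizes rest on the Youden criterion and binormal equal-variance markers; another criterion, or skewed or tied assay values, would change them. The direction of the bias follows from choosing the threshold by maximisation in the same data.

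**What to change.** State, in the protocol or the analysis plan, the criterion that defines the optimal cut-off. For any accuracy reported at a data-selected cut-off, give bootstrap optimism-corrected sensitivity, specificity and Youden index, re-selecting the cut-off in every resample, with intervals that reflect the selection. Label the cut-offs exploratory until they have been tested in new patients. Leave the AUC comparisons as planned.

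The cost is a few lines of Stata code and no extra patients. Reported accuracy will be slightly lower. The correction removes most of the bias but not all of it, which is a further reason for the exploratory label.

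### The two AUC sample sizes cannot both give 80% power from one set of assumptions: pyelonephritis has a null AUC of 0.6 that does not fit the stated 0.7-to-0.8 target, and fewer cases than pneumonia

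*Protocol*

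**What the plan says.** The protocol, under *Diagnostic value of infection markers*, plans to compare PCT, CRP and suPAR by ROC curves. Its sample size sentence opens with a single aim for both diseases: to "find a difference in Area under the curve (AUC) from 0.7 to 0.8 between two tests". Two sizes follow, at the same power and alpha:

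- Pneumonia: "200 verified pneumonia cases and 200 controls (power 0.8, alpha 0.05, AUC below 0 hypothesis 0.7".
- Pyelonephritis: "150 verified pyelonephritis cases and 150 controls (power 0.8, alpha 0.05, AUC below 0-hypothesis 0.6".

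The sentence gives no sidedness, no correlation between the two AUCs being compared, and no separate alternative AUC for pyelonephritis. It cites a web tool for the calculation but not the inputs entered.

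Two other sections bear on this. *Patient characteristics and course of treatment* gives the same case counts, 200 and 150, from an events-per-variable rule. *Outcomes and statistical analysis* expects at least 250 pneumonia and at least 150 pyelonephritis diagnoses.

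**The concern.** The sentence conflicts with itself in two ways. A null of 0.6 is not part of a comparison of 0.7 with 0.8. And if the intended difference is still 0.1, the two sizes are in the wrong order: the variance of an estimated AUC rises as the AUC falls towards 0.5, so a comparison starting at 0.6 needs more patients than one starting at 0.7, yet the plan gives it fewer.

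At stake is the stated power for the pyelonephritis half of objective 2. Pneumonia has a margin (250 expected against 200 required). Pyelonephritis has none (150 against 150), so an error in the 150 is not absorbed elsewhere in the plan.

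**Working it through.** **Inputs from the protocol.** Power 0.80, alpha 0.05, one control per case; AUC 0.7 versus 0.8; null AUC 0.7 (pneumonia) and 0.6 (pyelonephritis); 200 and 150 cases.

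**Assumptions, because the protocol is silent.** One- or two-sided test; correlation r between the two AUCs from 0 to 0.6; variance by Hanley-McNeil or by the binormal approximation.

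**Formula.** Cases per group for AUCs A1 and A2:

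n = [z_alpha·√V0 + z_beta·√VA]² / (A1 − A2)²

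with V0 = 2(1 − r)·V(null) and VA = V(A1) + V(A2) − 2r·√(V(A1)·V(A2)).

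The Hanley-McNeil variances, per case with equal groups, are V(0.6) = 0.1586, V(0.7) = 0.1349 and V(0.8) = 0.0978.

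**Step 1: the pneumonia figure** (two-sided, r = 0, 0.7 versus 0.8).
(1.96·√0.2699 + 0.8416·√0.2327)² / 0.01 = (1.018 + 0.406)² / 0.01 ≈ 203.
The binormal variance gives 222 at r = 0 and 199.5 at r = 0.1. So 200 reproduces for a two-sided test with r about 0 to 0.1.

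**Step 2: the same calculation for pyelonephritis** (0.6 versus 0.7).
(1.96·√0.3171 + 0.8416·√0.2935)² / 0.01 = (1.104 + 0.456)² / 0.01 ≈ 243.
Binormal: 242. If 0.7 versus 0.8 is kept and 0.6 is used only for the null variance, the need is 228 to 233.

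**Step 3: power with 150+150** (0.6 versus 0.7, two-sided, r = 0).
(0.1·√150 − 1.104) / √0.2935 = 0.121 / 0.542 = 0.223, so power is 0.59.
Across both variance formulas, both readings in step 2 and r from 0 to 0.1, power is 0.59 to 0.65.

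**Step 4: other assumptions.** Each cell shows Hanley-McNeil / binormal.

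| Test, r | n, 0.7 v 0.8 | n, 0.6 v 0.7 | Power at 150, 0.6 v 0.7 |
|---|---|---|---|
| Two-sided, 0 | 203 / 222 | 243 / 242 | 0.59 / 0.59 |
| Two-sided, 0.1 | 183 / 200 | 219 / 218 | 0.64 / 0.64 |
| Two-sided, 0.4 | 122 / 133 | 146 / 145 | 0.81 / 0.81 |
| One-sided, 0 | 159 / 174 | 191 / 190 | 0.71 / 0.71 |
| One-sided, 0.2 | 127 / 139 | 153 / 152 | 0.79 / 0.80 |

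In every row the 0.6 null needs more cases than the 0.7 null. Where 150 is about right for pyelonephritis, pneumonia needs about 122 to 139, not 200.

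**Step 5: other readings of the 0.6.**

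- *0.6 versus 0.8* (two-sided, r = 0): (1.104 + 0.8416·√0.2563)² / 0.04 ≈ 59. Power with 150 is above 0.99, so 150 does not fit.
- *0.6 as a misprint for 0.7*: both lines then have identical inputs and must give the same size. With r set so that 200 is exact, 150 gives power of about 0.67.
- *One marker against a fixed value of 0.6, alternative 0.7*: about 119 needed. This is not a comparison of two tests, and the matching pneumonia figure would be about 97 to 108.
- *A larger alternative*: from 0.60, uncorrelated and two-sided, 150+150 has 80% power for an AUC of about 0.73. The protocol does not state this value.

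**The case against.** The strongest reply is that none of this proves a shortage of power. The protocol fixes neither sidedness nor correlation nor a pyelonephritis alternative. The three markers come from the same patients, so a positive correlation is to be expected, and for a two-sided 0.10 difference the uncorrelated 0.59 is then a lower bound. At r = 0.4, 150+150 gives about 0.81, and 200+200 gives 0.93 to 0.95, which would make the pneumonia size merely generous. The correlation could also differ between diseases. The cited tool's formula and settings are not visible, so the assumptions that reproduce 200 are inferred.

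All of that stands, and it limits the claim. A reader might infer that the pyelonephritis comparison has about 60% power. The document does not support this as a fact, because it depends on choices the protocol does not make. Nor is it true without conditions that 0.7 versus 0.8 misses 80% with 150+150: at r = 0.35, two-sided, it reaches 0.82 to 0.85. Nor is a null of 0.6 harder in itself; against an alternative of 0.8 it is easier.

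The reply does not remove the contradiction. Disease-specific correlations or alternatives could give 200 and 150, but the protocol states none, and its one stated target excludes a 0.6 null.

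**Conclusion.** The contradiction holds. The 0.6 null does not match the announced effect, and no common choice of sidedness, variance formula and correlation that was tried (r from 0 to 0.6) makes both 200 and 150 the 80%-power sizes. For a 0.1 difference, the 0.6 null needs about 9% more cases (binormal) to 20% more (Hanley-McNeil) than the 0.7 null; the plan gives 25% fewer.

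The size of any power deficit is conditional. With the assumptions that reproduce about 200 for pneumonia (two-sided, r about 0 to 0.1, difference 0.1), the pyelonephritis comparison needs about 205 to 243 cases and 150 gives power of about 0.59 to 0.65. About 0.80 is reached if r is about 0.35 to 0.4 (two-sided) or about 0.2 (one-sided), or if the alternative is about 0.73.

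A reader might also infer that 150 was carried over from the events-per-variable rule. The matching counts suggest it but do not prove it.

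**What to change.** In *Diagnostic value of infection markers*:

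1. Give each disease its own null and alternative AUC, and correct the pyelonephritis pair so that it agrees with the opening target, or change the target.
2. State whether the test is one- or two-sided, and one assumed correlation between AUCs for both diseases, with a range.
3. Recompute both sizes as paired AUC comparisons (DeLong), because PCT, CRP and suPAR are evaluated for the same diagnoses in the same patients.
4. Restate the power, or the AUC difference detectable at 80% power, that 150 pyelonephritis cases give. Do not simply write in 0.59, which is an uncorrelated figure for paired markers.

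The cost is one recalculation and a few lines of protocol text, with no change in enrolment. The drawback is that the stated pyelonephritis power may become less favourable.
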